**8.4 STUDY PROCEDURES**

Five steps will be sequentially rolled out across the 4 hospitals over 13 months: **1. Set up** ensures adequate training and collection of control and intervention data. **2. Control steps**-are usual care, i.e., standard silver dressings. **3.** **Intervention establishment** involves the research nurses (ReNs) collaborating with the NAG and local champions to promote the INPREP Pathway and delivering the companion implementation strategies. A project manager will develop a study manual and training schedule for ReNs, monitor data integrity, intervention fidelity log and collaborate with the team (ReNs and CIs) to promote intervention fidelity. **4. Implementation period** is intervention exposure. **5. Sustainability** of adherence measured. In both control and implementation steps other burn care will be as per local standards (40). Implementation education will provide evidence-based advice, but treating clinicians will determine definitive care (e.g., inpatient versus outpatient care) based on patient needs and healthcare priorities.

**Figure 2.** Steps for the multi-centre, prospective, pragmatic, stepped-wedged randomised controlled trial

[figure not shown]

**Figure 2**. Illustrates the five steps of the multi-centre, prospective, pragmatic, stepped-wedged randomised controlled trial that will be conducted across the four participating paediatric hospitals. Following initial set up, all participating sites will start the trial in control phase with the baseline measures taken, and then one site will randomly step up (computer-generated, centralised randomisation) to implementation every 6 weeks, until saturation of the implementation intervention across all sites.

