**12. STATISTICAL CONSIDERATIONS AND DATA ANALYSIS**

**12.1 Sample size and statistical power**

Our project follows a pragmatic design to best allow the NPWT Pathway intervention to be tailored to the site context. The study will be conducted across four state’s tertiary paediatric burns centres. All sites will start the trial in control phase with the baseline measures taken, then one site will randomly be allocated (i.e., NPWT implemented across the site) (using computer-generated, centralised randomisation) to implementation every 6 weeks, until the new intervention has been implemented across all sites at 13 months. At 13 months after implementation has occurred across all sites, adherence sustainability will be measured to inform implementation effectiveness. Using a step wedge study design, and four sites with a minimum of 100 individuals recruited from each site (recruiting patients until the capacity of the site is reached), we would be able to detect a difference of 10% in adherence rate with 94% power (5% alpha). We expect an improvement of 10% in adherence from 10% in controls to 20% in the treatment. A greater difference in adherence, with the same parameters otherwise, will result in higher power and thus the above is the minimum numbers expected. Calculations were performed with the shiny app from Hemming et al. (2015) (38). We anticipate a minimum of 120 potential patients per site, which will be more than the above estimate and thus the power of this study is expected to be >94%.

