**12.2 Statistical analysis methods**

Generalised Linear Mixed Models (fitting a random intercept to account for clustering, random effect) and Generalised Estimating Equations (using the individual as the clustering unit) will be used to compare the effect of switching from the usual care to INPREP condition on primary and secondary outcomes. Specifically, an appropriate protocol for model selection based on Zuur *et al*. (2009) will be applied (49). This analysis approach is able to account for potential temporal trends, using time as a covariate, in addition to clinical explanatory variables (total body surface area, age, gender), which will be included in each model. It should be noted that other covariates, such as time, could be used as random effects in the mixed models.

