**12.2.2 Cost effective analysis**

## We will record data, analyse, and report cost-effectiveness findings following guidelines for trial-based cost-effectiveness analyses (50), including reporting resource use and costs (healthcare perspective) for each trial condition. Healthcare utilisation data will be costed using actual costs (e.g., device costings) when available or market rates. Intervention provision costs to deliver usual care or INPREP during the trial (12-month time-horizon for patients) will be recorded and applied at a per-patient level. A trial-based incremental cost-effectiveness ratio (ICER) will be estimated for the incremental cost per additional patient successfully completing NPWT. ICER=[(CostNPWT) minus (Costusual care)] / [(EffectNPWT minus Effectusual care)]. Due to the potential for uncertainty and non-normal distributions, 95%CIs (for costs and effect estimates) and a 95% confidence ellipse (for ICER) will be derived from bootstrap resampling. In addition, Markov modelling (5-year time-horizon) will be used to extend these cost-effectiveness findings by generating estimates for the consequences (on costs and patient outcomes listed above) of implementing INPREP at all specialist paediatric hospitals in Australia using data from this trial and prior studies as well as health service and population profile data (e.g. Australian Bureau of Statistics). In addition to probabilistic sensitivity analyses, we will assess sensitivity of results to variation in measured resource use, unit costs, effectiveness, time-horizon, and discounting (one way and multi-way sensitivity analyses).

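### One of the two analyses named for the primary outcome, the GEE, clusters on the child although hospitals are randomised; the mixed model's grouping factor and the primary method are left unnamed

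*Protocol*

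**What the plan says.** Section 12.2 gives two methods in one sentence, both for the primary and the secondary outcomes. The first is "Generalised Linear Mixed Models (fitting a random intercept to account for clustering, random effect"). The second is "Generalised Estimating Equations (using the individual as the clustering unit) will be used to compare the effect of switching" from usual care. The grouping factor of the random intercept is not named, and neither method is called primary. The covariates are listed as "using time as a covariate, in addition to clinical explanatory variables (total body surface area, age, gender), which will be included in each model". Site is not in that list.

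The randomised unit is the hospital. Section 8.4 says "one site will randomly step up (computer-generated, centralised randomisation) to implementation every 6 weeks", and section 12.1 repeats it: "one site will randomly be allocated (i.e., NPWT implemented across the site"). The planned size is "four sites with a minimum of 100 individuals recruited from each site", and section 12.1 adds: "We anticipate a minimum of 120 potential patients per site".

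The primary outcome in section 8.3.1 is the rate of patients treated according to the pathway, so each child contributes one yes/no value.

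**The concern.** When every cluster holds one observation, a GEE's robust standard error is that of an analysis of independent children. Nothing else in the stated GEE carries hospital differences, because site is not a covariate.

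In a stepped wedge, hospitals that cross early contribute more intervention time than those that cross late. Without a site term, a standing difference between hospitals feeds into the estimated effect of the pathway, and the standard error makes no allowance for it. Section 2.3 reports that NPWT use already differs between the services, so some between-hospital correlation in adherence is to be expected, although the protocol does not say how much.

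At stake is the test of the primary hypothesis. If the GEE carries it, p-values are too small and intervals too narrow. If the mixed model carries it, this depends on the unnamed grouping factor being the hospital.

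**Working it through.** **Inputs from the protocol.** 4 sites; 100 children per site (120 anticipated); one site crossing per step; 10% control adherence, 20% under the pathway; 5% alpha.

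**Assumed, because the protocol does not give them.** 5 periods (9 as a sensitivity case); ICC from 0 to 0.10; correlation within a site constant over time unless stated; alpha two-sided. The ICC is what remains after covariate adjustment. The calculation adjusts for period only, not for burn area, age or gender.

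**Can the ICC be recovered from the stated 94% power?** No. The usual stepped-wedge variance formula with 100 per site and 5 periods gives 52% power at ICC 0 and 39–44% at ICC 0.01 to 0.10. It reaches 94% only at an ICC of about 0.81. The figure does fit if 100 is read as children per site per period (95–96%). That is a separate sample-size question, and it leaves the ICC unidentified.

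**Variance ratio.** Let X be the treatment indicator for site i in period t, z = X minus the mean of X over sites in that period, and m the children per site-period. If children are treated as independent but sites share an ICC of ρ, the ratio of true to reported variance of the treatment effect is

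r = (1 − ρ) + m·ρ·[Σ over sites of (Σ over periods of z)²] / Σz².

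For 4 sites and 5 periods the site totals of z are 1.5, 0.5, −0.5 and −1.5. Their squares sum to 5. Σz² = 4 × (0.1875 + 0.25 + 0.1875) = 2.5. The bracketed ratio is 5/2.5 = 2, so r = 1 − ρ + 2mρ. The ratio is also 2 with 9 periods.

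- 100 per site, 5 periods: m = 20, r = 1 + 39ρ
- 120 per site, 5 periods: m = 24, r = 1 + 47ρ
- 100 per site, 9 periods: m = 11.1, r = 1 + 21.2ρ

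**Type I error** = 2 × [1 − Φ(1.96/√r)]. Example at ρ = 0.02, m = 20: r = 1.78, 1.96/1.334 = 1.469, type I error 14.2%.

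| Assumed ICC | 100/site, 5 periods | Logistic simulation, same setting | 120/site, 5 periods | 100/site, 9 periods |
|---|---|---|---|---|
| 0 | 5.0% | 5.0–5.6% | 5.0% | 5.0% |
| 0.01 | 9.6% | 10–12% | 10.6% | 7.5% |
| 0.02 | 14.2% | 14–15% | 15.9% | 10.1% |
| 0.05 | 25.4% | 22–24% | 28.4% | 17.2% |
| 0.10 | 37.6% | 31–34% | 41.2% | 26.7% |

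The simulation used 10% adherence, no true effect and up to 2,500 runs per setting. Runs with an empty site or period were dropped: about 18–19% of runs at ICC 0.10, so that row is approximate.

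**Alternatives in the same simulation.**
- Site as a fixed effect plus period: 3–5% when the within-site correlation is constant over time, 6–11% when it decays between periods (cluster autocorrelation 0.8).
- GEE clustered on site with the uncorrected sandwich: 23–36%, because there are only four clusters.
- Permutation over the 4! = 24 site orders: the smallest attainable p is 1/24 = 0.042. Type I error stays below 5%, but power for 10% versus 20% at 20 per site-period is about 21%.

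**The case against.** The strongest reply is that the same sentence opens with a mixed model whose random intercept is there to account for clustering. The plan does not overlook clustering, and a mixed model grouped by hospital would not have this fault. That stands. A reader might infer that every standard error and p-value for the primary outcome will be wrong; the text does not support it, because it does not say the GEE carries the primary inference.

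Second, the size of the inflation is not a figure from the protocol. It is nil at ICC 0, about 1.5- to 2-fold at 0.01, and reaches 3-fold only from about 0.023 with five periods. Section 2.3 says practice varies but gives no amount. That stands too. A flat claim of several-fold inflation would go beyond the document, as would rates based on 100 children in every site-period (about 2,000 in all), when section 12.1 speaks of 400 to 480.

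Third, clustering on the child is sensible for measures repeated within a child, such as the pain scores that Appendix 5 schedules at successive dressing changes. True, but section 12.2 applies the GEE to the primary outcome as well, and repeated measures within a child would still need site in the model.

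Fourth, the primary model and small-sample corrections are often settled in a statistical analysis plan. As omissions they would be no finding. The clustering unit, however, is stated, and stated wrongly for the primary outcome. One might extend the point to the bootstrap in section 12.2.2, but there the resampling unit is simply not given, which is detail a later plan can supply.

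**Conclusion.** The point holds for the GEE. For an outcome recorded once per child, the clustering unit in section 12.2 makes it an independence analysis in a trial that randomises four hospitals, and it overstates precision whenever adherence is correlated within hospitals. At the stated minimum size and five assumed periods, a nominal 5% test would reject in about 10% of null trials at ICC 0.01, 14% at 0.02, 25% at 0.05 and 31–38% at 0.10. With nine periods the rates are 7.5%, 10%, 17% and 27%. All of these rest on assumed ICCs and period counts.

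The mixed model is not shown to be wrong. It is incompletely specified, and because no method is primary, a flawed test and a possibly sound one stand side by side for the same hypothesis. This should be settled before analysis.

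**What to change.** In section 12.2, or in a statistical analysis plan that expressly supersedes it:

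1. Remove the statement that the individual is the GEE clustering unit for outcomes recorded once per child. Keep child-level clustering only for repeated measures within a child, with site still in the model.
2. Name one primary analysis for adherence: the mixed model with site as the grouping factor and period as a categorical effect, beside the listed covariates.
3. Add a site-by-period term as a sensitivity analysis, since site and period effects alone gave 6–11% when correlation decays over time.
4. State a small-sample reference for four clusters, such as a t distribution with small-sample degrees of freedom. Changing the GEE unit to site with the usual sandwich is not a repair.

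The change is wording only, with no new data. The price is wider intervals and lower power: model-based power at 100 per site is about 39–44% at ICC 0.01 to 0.10, against 52% at ICC 0. A permutation test protects the error rate but, at about 21% power and a minimum p of 0.042, suits a sensitivity check rather than a required primary test.

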| **The research team have conducted a series of studies, the findings of which** supports the components and implementation of this work (13, 26, 31).   - **We demonstrated the efficacy of the adjunctive use of NPWT for acute paediatric burns** in a RCT at Queensland Children’s Hospital (n=114) (26). When incorporated with the use of standard silver impregnated dressings, NPWT **improved time to wound closure** by 22% (95% CI 7-34, p=0.005). Patients who received NPWT had a 60% (95% CI 18-81, p=0.013) **reduced risk of long-term scar management** referral. A post hoc subgroup analysis suggests NPWT applied within 48 hours of the burn injury may provide even greater therapeutic benefits. - **We conducted a trial-based economic evaluation** from the healthcare provider perspective, prospectively recording resource usage and costs from the first visit to six-months following injury. Total mean healthcare costs for children who received **NPWT** **were lower** than standard silver dressings ($903.69 vs $1669.01) (13).   **[figure not shown]**   - The greatest reductions were **related to scar management and operative interventions**. Primary analysis indicated that there was an **89% probability** **that** **NPWT was dominant** (lower costs and faster wound healing) (Figure 1). - **We were the first to characterise the proteome of wound fluid collected via NPWT (31)**. We identified and quantified the NPWT fluid constituent proteins using liquid chromatography tandem mass spectrometry and compared them to the proteome of matched paediatric burn wound exudate samples. Several proteins were more abundant in the NPWT fluid, including proteases and immune/inflammatory proteins. The results **support the hypothesis that NPWT augments wound healing through the modulation** of factors involved in the inflammatory response, granulation tissue synthesis, and extracellular matrix maintenance (31). More samples need to be collected to comprehensively understand the biological mechanism behind the effectiveness of NPWT.   ***Figure 1*** *Incremental cost-effectiveness of adjunctive NPWT versus standard care with 95% confidence ellipse* |
| --- |

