**5.2 Secondary Hypotheses**

Secondary hypothesis: Paediatric patients with burns treated in the implementation phase will heal significantly faster resulting in reduced surgical requirements, scar treatment referrals and overall healthcare costs per patient compared to those treated in the control phase.

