***Secondary Patient Outcomes:***

1. *Healing outcomes:* i) Time/days to re-epithelialisation (blinded photo assessment), ii) skin grafting requirements, iii) burn wound exudate, iv) number of dressing changes, v) adverse events (26).
2. *Operating theatre requirements:* i) proportion patients requiring an operation (%), ii) operations required per patient, iii) operative procedures performed (e.g., skin graft) (26).
3. *Hospital requirements 12 months post-injury:* i) proportion of patients needing ≥1 admissions to hospital (% & length of stay), ii) number of outpatient appointments, iii) number of scar clinic appointments.
4. *NPWT device malfunctions:* i) alarms ii) charging issues

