**Appendix 5. Schedule of Assessments**

| Visit | Initial Presentation | COD1 | COD2, COD3…^1^ | Surgical intervention | 3 months | 12 months |
| --- | --- | --- | --- | --- | --- | --- |
| Eligibility and consent |  |  |  |  |  |  |
| Eligibility screen | X |  |  |  |  |  |
| Signed informed consent | X |  |  |  |  |  |
| REDCap data collection forms |  |  |  |  |  |  |
| Demographic and Injury Details | X |  |  |  |  |  |
| Initial Presentation | X |  |  |  |  |  |
| First Change of Dressing |  | X |  |  |  |  |
| Ongoing Dressing Changes |  |  | X |  |  |  |
| Surgical Interventions & Requirements |  |  |  | X |  |  |
| Completion Data |  |  |  |  |  | X |
| Additional data points |  |  |  |  |  |  |
| Time taken to complete dressing | X | X |  |  |  |  |
| % Re-epithelialised | X | X | X | X |  |  |
| Burn depth re-assessment |  | X |  |  |  |  |
| Photos^2^ | X | X | X | X |  |  |
| Pain scales |  |  |  |  |  |  |
| Clinician pain scales – FLACC/NRS^3^ |  |  |  |  |  |  |
| Baseline | X | X | X | X |  |  |
| Peak procedural | X | X | X |  |  |  |
| Parent-proxy pain scales - NRS |  |  |  |  |  |  |
| Baseline | X | X | X | X |  |  |
| Peak procedural | X | X | X |  |  |  |
| Patient pain scales – FACES^4^ |  |  |  |  |  |  |
| Baseline | X | X | X | X |  |  |
| Peak procedural | X | X | X |  |  |  |
| Implementation outcomes^5^ |  |  |  |  |  |  |
| Clinician | X | X |  |  |  |  |
| Parent-Guardian |  | X |  |  |  |  |
| Biological Samples |  |  |  |  |  |  |
| Urine Sample | X | X |  |  |  |  |
| Blood Sample^6^ | X | X | X | X |  |  |
| Wound Fluid | X | X^7^ |  |  |  |  |
| Hair Sample | X |  |  |  | X |  |

COD = change of dressing; FLACC = face, legs, activity, cry, consolability; NRS = numeric rating scale; FACES = faces pain scale – revised

^1^ Every change of dressing until patient is 95% re-epithelialised.

^2^ Wound photos to be taken after debridement but before dressing application.

^3^ FLACC to be collected if patient under 7 years of age, NRS to be collected if patient ages 7 or over.

^4^ Patient pain scales only required for patients aged 7 years or older.

^5^ Implementation outcomes only required for patients enrolled in the intervention arm.

^6^ Only if patient is already cannulated or undergoing procedure under a general anaesthetic.

^7^ Only if patient in intervention arm and wound fluid able to be collected from NPWT device tubing.

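### Burn depth at presentation is not among the covariates that section 12.2 commits to each model, so the healing comparison is open to modest within-site shifts in depth mix

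*Protocol*

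**What the plan says.** Section 12.2 uses mixed models and generalised estimating equations to "compare the effect of switching from the usual care to INPREP condition on primary and secondary outcomes". It adjusts for time as a covariate and adds "clinical explanatory variables (total body surface area, age, gender), which will be included in each model". It also invokes a model-selection procedure taken from a cited textbook on mixed models, without saying which further variables that procedure may consider. Burn depth appears nowhere in the section.

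The outcomes served by these models include "Time/days to re-epithelialisation (blinded photo assessment), ii) skin grafting requirements" (section 8.3.2). Section 5.2 frames the clinical hypothesis as a comparison of phases: "Paediatric patients with burns treated in the implementation phase will heal significantly faster resulting in reduced surgical requirements".

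On data, Appendix 5 lists "Burn depth re-assessment" at the first change of dressing and a demographic and injury form at initial presentation. The contents of that form are not shown, and no depth item at presentation is listed by name.

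On design, section 8.4 has one of four sites, chosen at random, cross to implementation every 6 weeks. The study population paragraph after section 8.1 sets broad eligibility with no depth limit and leaves the detailed criteria to Phase 1.

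**The concern.** The protocol is not silent on clinical covariates. It picks three and commits them to every model. A baseline characteristic that plausibly drives healing time, grafting and scar treatment is not among them, although the schedule shows that depth is assessed.

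In an individually randomised trial, an omitted prognostic variable costs mainly precision. Here the unit of allocation is the site and there are four of them. Control and implementation patients are different children, seen in different weeks. A random intercept (read here as a site intercept) absorbs stable differences between hospitals in depth mix, and a time term absorbs trends common to all hospitals. Neither absorbs a change in depth mix within a site at about the time it crosses over. Section 8.4 describes no concealment of the phase from the staff who approach families, so a change in who is recruited at crossover is possible, though the protocol does not predict one. Such a change would be read as an effect of the Pathway on healing.

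TBSA and age would pick up only the part of a depth shift that is correlated with them.

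**Working it through.** The protocol gives no figure for depth, for phase-level healing or for grafting. Its one design calculation, 94% power, concerns adherence and does not enter here. The check therefore asks how large a shift in depth would have to be to imitate the healing effect that the protocol's own numbers imply.

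**Inputs from the protocol**
- Per-patient effect of NPWT on time to closure: 22% shorter, 95% CI 7 to 34 (summary of the team's earlier randomised trial, after section 2.3).
- Adherence: "We expect an improvement of 10% in adherence from 10% in controls to 20% in the treatment" (section 12.1).

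**Assumed inputs**
- R, the ratio of healing time in deeper to shallower burns: 1.25 to 2.5, with 1.5-2 as the central range.
- Share of residual variance in log healing time explained by depth: 20-40%.
- Prevalence of deeper burns: 10-30%.

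**Step 1. Implied phase-level effect**, treating adherence as receipt of NPWT.
- Arithmetic scale: 1 - (1 - 0.22 × 0.20)/(1 - 0.22 × 0.10) = 1 - 0.956/0.978 = 2.25%.
- Log scale: 1 - exp(0.10 × ln 0.78) = 2.5%.
- Arithmetic scale at the confidence limits (7% and 34%): 0.7% to 3.5%.

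**Step 2. Shift in the share of deeper burns that gives a 2.25% difference when depth is omitted**: shift = -ln(1 - 0.0225)/ln R.

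| R (assumed) | Shift needed |
|---|---|
| 1.25 | 10.2 points |
| 1.5 | 5.6 points |
| 2 | 3.3 points |
| 2.5 | 2.5 points |

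**Step 3. The reverse view**: apparent reduction in healing time = 1 - exp(-shift × ln R).
- 5-point shift: 1.1% (R = 1.25), 2.0% (1.5), 3.4% (2), 4.5% (2.5).
- 10-point shift: 2.2%, 4.0%, 6.7%, 8.8%.

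**Step 4. Sensitivity to the size of the true effect**
- Against the full 22%, the shift needed is 61 points at R = 1.5, 36 at R = 2 and 27 at R = 2.5. At R = 1.25 no shift is large enough.
- If adherence rose by 20 points instead of 10, the phase-level effect would be 4.5% and the shift needed 11.4 points (R = 1.5) or 6.6 points (R = 2).
- At a 50-point gain the effect would be 11.25% and the shift needed 29 or 17 points.

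**Step 5. Chance imbalance, for scale.** With 200 against 200 independent patients, the standard deviation of the difference in share is sqrt(2p(1 - p)/200): 3.0 points at p = 0.10 and 4.6 at p = 0.30. This is sampling error, already reflected in the unadjusted standard error. For this part, adjustment buys precision and does not remove bias.

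**Step 6. Precision for log healing time**: 1 - sqrt(1 - R²), where R² is the share of variance explained. This gives 10.6% at 0.20 and 22.5% at 0.40. It applies to a linear model of log time and to the part of the standard error that comes from patient-level residual variation.

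**The case against.** The strongest reply has five parts.

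- **Scope.** A complete covariate list for secondary outcomes is normally settled in the analysis plan, which is not at hand, and section 12.2 does not say that only these three variables may enter. This stands in part. A reader might infer that the covariate set is closed and depth excluded, but the wording supports only a committed minimum with a model-selection step beside it. The point survives because the protocol itself chose the clinical covariates, and leaving depth to data-driven selection is weaker than naming it.
- **Magnitude.** A reader might infer that depth shifts would exceed the expected effect. The documents do not support that. They give no depth distribution, no healing time by depth and no phase-level healing effect. The 2.25-2.5% is constructed from two protocol figures. A 5-point shift at R = 1.5 gives 2.0%, which is below it. Adherence in section 8.3.1 depends on both eligibility and duration, so a non-adherent child may still have received NPWT. Section 12.1 also contemplates a larger adherence gain.
- **Model.** Site and time terms, TBSA and age already deal with part of any shift in depth. This stands: only a within-site, off-trend shift remains, and the documents neither state nor forecast one.
- **Binary outcomes.** It is tempting to say that omitting depth widens every interval. It does not. In a logistic model, adjusting for a prognostic covariate does not shrink the standard error of the log-odds ratio and can raise it. Nor is there any grafting rate or expected grafting effect to compare with.
- **Adherence.** The primary outcome is adherence, and nothing here shows that its model needs depth.

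**Conclusion.** The point holds in limited form. Presentation depth is not among the covariates committed to each model, although the schedule implies that it is assessed, and crossover of four sites does not protect the healing comparison from a depth shift that coincides with it.

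For healing time, a shift of about 3-6 points in the share of deeper burns would match the implied phase-level effect of roughly 2.25-2.5%. This rests on an assumed healing ratio of 1.5-2 and on the 10-point adherence gain. It would come nowhere near the per-patient 22%, and it matters less the more adherence rises. The gain in precision for healing time, about 11-23% off the standard error, rests on an assumed 20-40% of explained variance.

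For grafting and scar treatment the argument is qualitative only: adjustment guards against a shift in case mix, with no figure for its size and no promised gain in precision. The primary analysis of adherence is not called into question.

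**What to change.** In section 12.2, or in the analysis plan before outcome data are examined by phase, add burn depth at initial presentation to the pre-specified covariates for the healing, grafting and scar-treatment models. Confirm that the presentation form records depth, and add the field if it does not. State that the depth re-assessed at the first dressing change will not be used in its place, since it is measured after exposure and may itself reflect treatment. The protocol does not propose that substitution, but it is the only depth item named in the schedule. Adding depth to the adherence model is optional.

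The cost is one covariate in the model statement and at most one form field. Sample size, visit schedule and treatment are unchanged, so this is a free improvement.
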